# Standardised Chinese herbal treatment delivered by GPs compared with individualised treatment administered by practitioners of Chinese herbal medicine for women with recurrent urinary tract infections (RUTI): study protocol for a randomised controlled trial

**DOI:** 10.1186/s13063-016-1471-5

**Published:** 2016-07-27

**Keywords:** Urinary tract infection, Chinese herbal medicine, Primary care, feasibility

## Abstract

**Background:**

In the UK, urinary tract infections (UTIs) are the most common bacterial infection presented by women in primary care. Recurrent urinary tract infections (RUTIs) are defined as three episodes of UTI in the last 12 months, or two episodes in the last 6 months. Between 20 and 30 % of women who have had one episode of UTI will have an RUTI, and approximately 25 % of these will develop subsequent recurrent episodes. RUTIs can have a significant negative effect on the quality of life, and have a high impact on health care costs as a result of outpatient visits, diagnostic tests and prescriptions. Chinese herbal medicine (CHM) has a recorded history of treatments for the symptoms of UTIs for more than 2000 years. More recent clinical research in China has provided some preliminary evidence that CHM can alleviate the symptoms of UTIs and reduce the rate of recurrence, but more rigorous investigation is required.

**Methods/design:**

The RUTI trial is a double-blind, randomised, placebo-controlled, feasibility trial. A total of 80 women will be randomised to ‘individualised’ herbs prescribed by a Chinese herbal practitioner or to ‘standardised’ herbs provided by primary care clinicians. Both arms will have herbs for prevention of UTIs and treatment of acute episodes. Treatment duration is for 16 weeks.

The primary outcomes are the number of episodes of recurrent UTIs during the trial period and in the 6 months of follow-up, and the number of days of symptoms rated moderately bad or worse based on patient diaries. Secondary outcomes will assess participant expectations and beliefs, adherence to the treatment, adverse events and health economics and provide quantitative and qualitative assessments of the impact of recurrent infections on the lives of women.

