## Methods/design

The trial has two separate but linked arms (see Additional file 1). Forty women from the Wessex, South and Northwest London and the Brighton and Hove areas of the Clinical Research Network (CRN) will be randomised to take traditional individualised herbal prescriptions following consultation with a registered CHM practitioner at a private clinic. Forty women from Wessex will be randomised to standardised ‘prescriptions’ of herbal capsules administered via nurses and doctors from GP practices. Both arms will have equal allocation to active and placebo medications. The trial is fully blinded with only the herbal dispensaries knowing the treatment allocation of the women.

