### Randomisation and blinding

Computer-generated block randomisation to either verum (active) or placebo CHM treatment will be performed with random block sizes of two, four, or six participants to ensure equal numbers in groups and to prevent the study team and the dispensary team from being able to predict a pattern to the randomisation.

In the standardised arm, this randomisation sequence will be used by the manufacturer to code the herbal capsules prior to the capsules being sent to GP practices. Capsules will be dispensed according to this sequence, and a record of the batch number recorded by the practice nurse.

For the individualised arm, the randomisation sequence will be stored at the herbal dispensary in opaque sealed envelopes and kept in a safe place only accessible to a designated person. On receiving the formula by email, this person will open the envelope and inform the herbal dispensary whether the trial participant is to receive the placebo or active herbs. A record of this allocation will be kept by the designated person so that repeat prescriptions will be allocated to the same arm.

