The RUTI trial is the first trial in the UK of a Chinese herbal remedy registered as an Investigational Medicinal Product. Obtaining ethical and regulatory approval has been a challenging educational and research experience for us as researchers and the various regulatory authorities with who we have worked closely in co-operation. Our first major outcome is that we have managed to negotiate the complex process successfully. This means that we have established a precedent to enable subsequent trials of CHM to take place. The RUTI trial is now recruiting, and we will be able to provide data on the feasibility and safety of using and researching CHM within primary care. This trial will also provide a comparison of individualised versus standardised herbal treatment that will help inform the design of future trials in herbal medicine. Finally, the RUTI trial will provide provisional estimates of the variance of change in continuous outcomes which, if warranted, could be used to inform a power calculation for a larger, more definitive trial for CHM as a treatment for RUTIs.

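### The article says women are randomised to individualised or standardised herbs, but the only randomisation it describes is verum versus placebo within each of two separate arms, so the between-arm comparison is non-randomised.

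*Protocol article*

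**What the plan says.** Three places state or suggest that women are randomised between the two forms of delivery.

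- The abstract's Methods/design paragraph says that "80 women will be randomised to ‘individualised’ herbs prescribed by a Chinese herbal practitioner or to ‘standardised’ herbs provided by primary care clinicians".
- The opening paragraph of Methods/design says "Forty women from the Wessex, South and Northwest London and the Brighton and Hove areas of the Clinical Research Network (CRN) will be randomised" to individualised prescriptions at a private clinic, and "Forty women from Wessex will be randomised to standardised" capsules given through GP practices.
- The title, which ends by calling the study a randomised controlled trial, names its subject as "Standardised Chinese herbal treatment delivered by GPs compared with individualised treatment administered by practitioners of Chinese herbal medicine".

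Other places describe a different structure. Methods/design says "The trial has two separate but linked arms", each with equal numbers on active and placebo. Randomisation and blinding says "Computer-generated block randomisation to either verum (active) or placebo CHM treatment will be performed", in blocks of 2, 4 or 6. In the standardised arm the manufacturer uses the sequence to code the capsules. In the individualised arm it sits in envelopes at the herbal dispensary, and an envelope is opened once the practitioner's formula has arrived.

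The Discussion then says "This trial will also provide a comparison of individualised versus standardised herbal treatment", which is meant to help inform later trials. Data analysis plans exploratory effect estimates for three categories (individualised, standardised, placebo), while the qualitative study under Secondary outcomes samples from four groups.

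**The concern.** The abstract's design sentence describes a randomisation that the Methods do not contain. A reader who takes it at face value will treat a difference between individualised and standardised treatment as protected by randomisation. On the procedure described, it compares two groups of women recruited through different routes and partly from different areas.

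The analysis could also be affected. The three-category wording in Data analysis is ambiguous: it may mean one combined placebo group. If so, and if arm is not adjusted for, each verum group would be compared partly with women from the other arm, who took a different placebo (sugar beet fibre capsules or flavoured granules). That would weaken the contrasts that are properly randomised.

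**Working it through.** **1. Sample size.** 40 + 40 = 80 women. Equal allocation to verum and placebo in each arm gives 4 groups × 20 = 80. This reproduces the stated total and agrees with the four groups under Secondary outcomes. No power calculation is given, so there is none to check.

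**2. What is randomised.**

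| Step | Standardised arm | Individualised arm |
|---|---|---|
| Recruitment area | Wessex | Wessex, South and Northwest London, Brighton and Hove |
| Route | GP practice | CHM practitioner at a private clinic |
| Carrier of the sequence | Capsules coded by the manufacturer | Envelopes at the dispensary |
| What the sequence decides | Verum or placebo | Verum or placebo |
| Route known when the sequence is applied? | Yes: capsules are already at the practice | Yes: the consultation has taken place and the formula is written |

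No step allocates a woman at random between the columns. Women outside Wessex can enter only the individualised arm, so a single randomisation of all 80 between routes is impossible as described.

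**3. Regional imbalance.** The Wessex share *w* of the individualised arm is not given. The number of its women with no regional counterpart in the standardised arm is 40 × (1 − *w*). The chance that a Wessex participant is in the individualised arm is 40*w* / (40*w* + 40).

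| *w* (assumed) | No regional counterpart | Chance for a Wessex participant |
|---|---|---|
| 0% | 40 | 0 |
| 25% | 30 | 0.20 |
| 50% | 20 | 0.33 |
| 75% | 10 | 0.43 |

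Region balances only if all 40 come from Wessex, which contradicts the stated catchment.

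**4. Precision of the difference between the two placebo-controlled effects.** The documents give no event rate, so these inputs are assumed: 4 UTIs a year in every group, negative binomial dispersion *k* = 0.5, 20 v 20 per arm, no dropout.

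- Expected count per woman: μ = 4 × weeks / 52
- SE of the log rate ratio within one arm: √[2(1/μ + *k*)/20]
- SE of the difference between two such log rate ratios: that value × √2
- 95% CI factor: exp(1.96 × SE)

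| Period | μ | SE within arm | SE of difference | CI factor |
|---|---|---|---|---|
| 16 weeks | 1.23 | 0.362 | 0.512 | 2.7 |
| 16 weeks + 6 months (42 weeks) | 3.23 | 0.285 | 0.402 | 2.2 |

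Over 3 to 5 UTIs a year and *k* from 0.3 to 1.0, the 16-week factor runs from about 2.35 (μ = 1.54, *k* = 0.3) to about 3.5 (μ = 0.92, *k* = 1.0).

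**The case against.** The strongest reply is that the true structure is disclosed. The abstract calls the trial placebo-controlled; Methods/design gives the two catchments and routes; Randomisation and blinding gives the mechanism for each arm. Data analysis says the trial is not powered for effects, calls their estimation exploratory and commits to controlling for important confounders. This stands as a limit on the consequences. It does not remove the conflict: the abstract and Methods/design still name a randomisation that is nowhere described, and adjustment does not make a contrast randomised.

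Four stronger readings are tempting, and the documents do not support them.

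- *The Discussion claims a randomised comparison.* It promises a comparison without calling it randomised. The title is suggestive only. The explicit wording is in the abstract and Methods/design.
- *Setting, consultation and formulation are confounders.* They belong to the two packages being compared; Research objectives itself asks about differences in delivery. The confounding at issue is by region and by who enters each route.
- *The result will be reported as randomised, and future trials will rest on it.* Data analysis labels effect estimates exploratory, and the Discussion claims only to help inform later design.
- *The difference between the two placebo-controlled effects is protected by randomisation.* Each within-arm effect is. Their difference still compares populations that were not randomised to each other and can reflect region or patient mix.

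**Conclusion.** The point holds as a contradiction about what is randomised. The abstract and Methods/design say women are randomised to a form of delivery, and the title suggests it; the procedure randomises only verum against placebo within each arm. The individualised-versus-standardised comparison is non-randomised.

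The size of any bias cannot be derived, because the documents give neither event rates by area nor the Wessex share. What can be said is that regional confounding is partial and that even the better between-arm estimate would be imprecise: a CI factor of about 2.7 over 16 weeks or 2.2 over 42 weeks, on the assumed rate and dispersion.

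It remains possible that Wessex women are randomised between arms, since Wessex feeds both, but no such step is described. Verum versus placebo within each arm is validly randomised and the feasibility aims are untouched. For an unpowered feasibility trial this should be corrected, at a severity below must-fix.

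**What to change.** - Reword the abstract and the opening of Methods/design: women are randomised 1:1 to verum or placebo within each delivery arm, and delivery arm is not randomised. Clarify the title and the Discussion sentence to match.
- Name verum versus matching placebo within each arm as the randomised contrasts, and do not pool the two placebo groups without adjusting for arm.
- Report individualised versus standardised only as exploratory and non-randomised. The preferable form is the difference between the two placebo-controlled effects (an arm-by-treatment interaction) with its CI, with a note that this difference is itself not protected by randomisation.
- If Wessex women are in fact randomised between arms, describe that step and limit the randomised between-arm contrast to them.

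The cost is a few sentences and, for the between-arm estimate, one model term. No extra women are needed. The downside is that the stated claim for the comparison becomes less favourable.

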**Discussion:**

The RUTI trial is the first instance of CHM delivered as a clinical trial of an investigatory medicinal product in the UK. This study provides important information regarding the feasibility and acceptability of researching and using CHM in Primary care. Once completed, it will provide provisional estimates of the variance of change in continuous outcomes to inform a power calculation for a larger, more definitive trial.

**Trial registration:**

EudraCT, 2013-004657-24. Registered on 5 September 2014.

**Electronic supplementary material:**

The online version of this article (doi:10.1186/s13063-016-1471-5) contains supplementary material, which is available to authorized users.

## Background

### Epidemiology and current management

In the UK, urinary tract infections (UTIs) are the most common bacterial infection presented by women in the primary care setting [1, 2], with approximately 40–50 % of women experiencing one episode during their lives [3]. This accounts for between 1–3 % of all consultations in general practice [4].

Recurrent urinary tract infections (RUTIs) are commonly defined in the literature as three episodes of UTI in the last 12 months or two episodes in the last 6 months [5]. Between 20 and 30 % of women who have had one episode of UTI will have a recurrent UTI and approximately 25 % of these will develop subsequent recurrent episodes [6, 7]. RUTIs can have a significant negative effect on the quality of life [8] and have a high impact on healthcare costs as a result of outpatient visits, diagnostic tests and prescriptions.

Antibiotics are currently the mainstay treatment for both acute and recurrent UTIs. Whilst antibiotics may be effective in reducing the duration of severe symptoms in acute episodes [9, 10], antibiotic resistance is currently estimated at 20 % for trimethoprim and cephalosporins and 50 % for amoxicillin [11]. Antibiotic resistance and previous episodes of cystitis have been positively associated with an increased duration of severe symptoms of UTIs [2]. It is predicted that antibiotic resistance will continue to increase [12]. The UK government and Chief Medical Officer for England have indicated the need to consider alternatives to antibiotics [13].

Antibiotic prophylaxis is, however, used to prevent RUTIs. Treatment usually lasts for between 6 and 12 months but can be extended for up to 5 years [14]. A Cochrane systematic review of antibiotics used to prevent RUTIs in non-pregnant women found that antibiotics given continuously for 6–12 months were significantly more able than placebo to prevent recurrent infection (RR 0.15 (95 % CI 0.08 to 0.28 and NNT 1.85 (CI 1.60 to 2.20)) [5]. However, more severe side effects were also experienced, requiring the withdrawal of treatment (such as urticaria, nausea and vomiting) and less serious but unpleasant side effects such as oral and vaginal candidiasis, and gastrointestinal disturbances resulting from antibiotic treatment. These can cause considerable discomfort and probably contribute to women’s expressed preference to avoid antibiotics use [15].

Once prophylaxis is discontinued, even after extended periods, approximately 50–60 % of women will become re-infected within 3 months [16, 17]. Thus, antibiotic prophylaxis does not exert a long-term effect on the baseline infection rate.

### Rationale for use of Chinese herbal medicine

Chinese herbal medicine (CHM) has a recorded history of treating the symptoms of UTIs for over 2000 years [18]. More recent clinical research in China has provided some supportive evidence that CHM can alleviate the symptoms of UTIs [19–22] and reduce the rate of recurrence 1 year post-treatment from 30 % when antibiotics were used alone to 4.4 % when antibiotics and CHM were combined [20]. A recent Cochrane review of CHM for RUTIs found some preliminary supportive data for herbal interventions, but the trials were of poor quality and further and more rigorous research was recommended [23].

### Rationale for the trial design

In accordance with MRC recommendations for the investigation of poorly evidenced complex interventions such as CHM [24], a strategic, phased, research-development process is essential. The RUTI trial has been conceived as a small scale feasibility trial to explore the treatment effects of CHM and to investigate if CHM can be used and researched in primary care.

### Research objectives

The key objectives for this study are as follows:To explore the feasibility of developing, implementing and evaluating a CHM intervention within the primary care networks with particular regard to recruitment, referral patterns, patient compliance, the use of a plausible herbal placebo and dropout ratesTo evaluate the acceptability and sensitivity to change of different outcomes measures and to provide a provisional estimation of any effect size relating to CHM treatment that could inform a more definitive future studyTo use nested qualitative research and quantitative quality of life outcome measures to explore the experience of women taking CHM and to investigate any perceived differences between the delivery of standardised remedies via GP practice nurses and individualised remedies via CHM practitioners

## Methods/design

The trial has two separate but linked arms (see Additional file 1). Forty women from the Wessex, South and Northwest London and the Brighton and Hove areas of the Clinical Research Network (CRN) will be randomised to take traditional individualised herbal prescriptions following consultation with a registered CHM practitioner at a private clinic. Forty women from Wessex will be randomised to standardised ‘prescriptions’ of herbal capsules administered via nurses and doctors from GP practices. Both arms will have equal allocation to active and placebo medications. The trial is fully blinded with only the herbal dispensaries knowing the treatment allocation of the women.

### Eligibility

A medical record search will be conducted for women who have had more than two prescriptions for trimethoprin or nitrofurantoin within the last 12 months and/or have been recorded as having recurrent UTIs.

A standard letter will be sent to these women with the Patient Information Sheet explaining the trial (Additional file 2). They will be contacted by the trial manager who will explain the trial more fully and assess eligibility. If the women are both eligible and interested an appointment will be made at the primary care site or at the appropriate clinic where written consent will be taken (Additional file 3).

### Inclusion/exclusion criteria

Women will be eligible for the trial if they meet all of the following criteria:are over 18 years and under 65 years of agehave reported three or more uncomplicated recurrent lower UTIs in the previous 12 monthshave had at least one episode documented as being suspected or confirmed as a bacterial UTI by a GP

Women will be ineligible if they have any of the following criteria:have symptoms of complicated UTIs, such as acute pyelonephritis.have known hepatic or renal diseaseare pregnant or breast feedinghave diabetesare taking drugs which may interact with Chinese herbal medicine: cardiac glycosides (digoxin), warfarin and lithiumhave psychosis, dementia or terminal illness that may prevent completion of the symptom diarieshave commenced a new treatment (conventional or complementary or alternative medicine (CAM)) for RUTIs in the previous 6 months.

### Randomisation and blinding

Computer-generated block randomisation to either verum (active) or placebo CHM treatment will be performed with random block sizes of two, four, or six participants to ensure equal numbers in groups and to prevent the study team and the dispensary team from being able to predict a pattern to the randomisation.

In the standardised arm, this randomisation sequence will be used by the manufacturer to code the herbal capsules prior to the capsules being sent to GP practices. Capsules will be dispensed according to this sequence, and a record of the batch number recorded by the practice nurse.

For the individualised arm, the randomisation sequence will be stored at the herbal dispensary in opaque sealed envelopes and kept in a safe place only accessible to a designated person. On receiving the formula by email, this person will open the envelope and inform the herbal dispensary whether the trial participant is to receive the placebo or active herbs. A record of this allocation will be kept by the designated person so that repeat prescriptions will be allocated to the same arm.

### Intervention

All women taking part will be able to consult with their GPs and, if necessary, use conventional medicines such as antibiotics for acute infections. Antibiotic use will be recorded as one of the trial outcomes. These can be taken in conjunction with the ‘acute’ herbal treatment.

Participants in the standardised arm will receive ‘acute’ and ‘preventative’ herbal capsules (Size 0, hypromellose capsules) to be used during and between instances of infection. Matching placebo capsules have been prepared containing therapeutically inert sugar beet fibre. In total, 16 weeks of preventative herbal capsules will be allocated to each participant, with an additional 4 weeks of ‘acute’ capsules to be used in the instance of a UTI occurring.

The individualised arm of the trial will follow routine practice of CHM, which involves a practitioner writing an individualised herbal prescription typically comprising between ten and 15 herbs selected from the Chinese herbal material medica. The selection of herbs is contingent upon a full CHM differential diagnosis made after a detailed consultation process. The formula used will also change over time to address the changing clinical presentation of the patient.

After the consultation with the CHM practitioner verum or placebo herbal medicines will be dispensed as concentrated herbal granules to be taken twice a day. Each dose will be separately packaged in a sealed foil sachet. These granules dissolve in hot water for patients to drink as an herbal decoction. The practitioner may allocate preventative treatment with a clearly labelled standby for an acute infection. Women allocated to placebo treatment will receive identically packaged granules derived from therapeutically inert food colourings and flavourings. Once re-constituted, these placebo herbs resemble the colour and the strong taste and smell of the verum formulae.

